### 6.6.2 Data Collection by Objective: Summary Outline

The following outline summarizes the organization and hierarchy of data to be collected under this protocol, and how each component contributes to the completion of our primary research objectives:

#### I. Objective 1

- a. Site Assessments (Rapid and In-Depth)
  - i. Community-Facility Linkage (CFL) model survey
  - ii. Structured Field Observations
    1. Public observations
    2. Private observations
  - iii. Focus Group Discussions (FGDs)
    1. Professional/ Lay Health Care Workers
    2. CFL Providers
  - iv. Managerial In-depth Interviews (IDIs)
    1. CFL Programme Site Supervisors & Regional / National Managers
    2. District Health Management Team Representatives

## II. Objective 2

- a. Chart Review (abstraction of existing programmatic data only)
- b. Nested Cohort (primary collection of study-specific data)
  - i. Biological outcome ascertainment
    - 1. Maternal
    - 2. Infant
  - ii. Structured client questionnaire
  - iii. Maternal in-depth interviews

### 6.6.3 Data Collection & Management Procedures

Routine MOH clinical and program records at study sites will be maintained in locked rooms per MOH standard operating procedures. These records contain identifying information, including name, date of birth, and addresses. Clinicians, Nurses, HSAs and Clerks are responsible for accurately filling the registers and treatment cards for clients during clinic visits. A trained and experienced UNC Data Associate will abstract existing clinical and demographic data from these routine data sources for the purposes of our retrospective cohort, and enter them into a secure Microsoft Access (Redmond, Washington, USA) database. Routine, existing data to be entered will encompass socio-demographic and clinical information, including documentation of HIV exposure, EID and HTC testing dates, and HIV rapid test, DNA PCR, and RNA PCR (i.e. maternal viral load) results, as well as baseline clinical data (e.g. WHO clinic stage), HCC and ART program enrolment dates, and ART initiation information (e.g. ART start date and ART regimen) for women found to be HIV-infected and their HIV-exposed/ HIV-infected infants.

All study-specific paper data on study forms, logs, registers, and other documents will be maintained in secure, locked filing cabinets in locked rooms at selected study sites and will only be accessible to study staff during working hours. In Lilongwe, these documents will be kept at the UNC Project Office situated on the grounds of Bwaila Hospital. In Neno, documents will be stored in a secure location at the Partners In Health Offices or the Neno District Health Office based on available space. In Mzimba North/South, Salima, and Zomba, study records will be stored securely in locked filing cabinets in a locked room identified by the DHO's office or CFL program partner. Once field-based study activities are completed, all study-specific forms will be stored at the UNC Project Office in Lilongwe. In all cases, personal identifying information and health information will be stored separately and will only be linkable through the use of a link log stored in a separate, secure location.

All electronic data will be saved onto encrypted password-protected computers and/or tablets and uploaded to the encrypted password-protected UNC Project server at regular intervals. Quality assurance and quality control procedures will be in place throughout the project, with regular assessment of missing or inconsistent records. We will conduct regular database queries of extreme and missing values. The PI, co-PI and the data manager (contact information above) will be ultimately responsible for all data security issues. All data will be stored per NHSRC guidelines. All identifying data will be purged from the database prior to creating the analytical dataset.

## 7.0 Data analysis

### 7.1 Study Outcomes

We will use routinely available program data for our retrospective cohort enriched by prospective nested cohort data to ascertain the following outcomes:

#### **Primary Outcome:**

- 12-month post-ART initiation retention in care for HIV-positive mothers

#### **Secondary Outcomes:**

- Proportion of pregnant women newly registered in ANC who received HIV testing services
- Proportion of HIV-infected PMTCT clients initiated on anti-retroviral therapy
- 6-month post-ART initiation retention in care for HIV-positive mothers
- Proportion of HIV-positive mothers achieving HIV virological suppression from 6 months post-ART initiation (at MOH-recommended times of 6 and 24 months post-ART and, through the study, at time points between 12 and 24 months post-ART initiation)
- 12-month infant HIV-free survival
- Exposed infant “early” HIV infection status (i.e. HIV-1/2 DNA PCR result) from age 6 weeks
- 24-month child HIV-free survival
- 12- and 24-month infant HIV sero-status
- Median time from PMTCT enrolment to maternal ART initiation
- Median age of ART initiation for HIV-infected infants and young children
- Proportion of HIV-infected infants and young children achieving HIV virological suppression (from 6 months post-ART initiation per MOH guidelines)

- Proportion of HIV-infected mothers and infants who “returned to care” within 30 and 60 days of meeting the national ART program definition of loss to follow-up/ “defaulting” (i.e. not known to have transferred out, stopped or died AND have not returned to the clinic for 2 months after the woman is expected to have run out of ARVs).
- Proportion of HEIs who “returned to care” within 30 and 60 days of meeting the national HIV Care Clinic (HCC) programme definition of loss to follow-up/ “defaulting” (i.e. not known to have transferred out, stopped or died AND have not returned to the clinic for 2 months after the “next appointment date” given at the last HCC visit).

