To improve MIP care retention in Malawi, several models have emerged to strengthen community-facility linkage (CFL), a concept defined as any “formalized connection between a health facility and the communities it serves to support improved health outcomes”. Similar to other SSA settings, three models have been widely implemented to complement Malawi’s National PMTCT Programme and enhance the standard of care (SOC). Under the current SOC, Ministry of Health (MOH) Health Surveillance Assistants (HSAs), a cadre that moves between clinics and decentralized “health posts” to enact a broad array of public health activities, support PMTCT clients primarily through health talks and tracing of MIPs who have defaulted from HIV care. However, HSA staffing levels are often insufficient to meet needs in the community (approximately 1 HSA per 1,000 households), and the resources and person-time available to HSAs to support dedicated PMTCT activities has historically been limited. In contrast, the three most common CFL models—1) mentor mothers; 2) expert clients; and 3) community health workers (CHWs)—mostly or exclusively have a PMTCT focus and offer intensive psychosocial support to PMTCT clients. Mentor and expert clients are types of peer health workers—women living with HIV who offer longitudinal health education and psychosocial support, often via peer group meetings, to PMTCT clients. CHWs are community-based health workers who provide clients with psychosocial support, promote medication and appointment attendance, accompany clients to health facilities for clinic visits, and support the services provided by other, often facility-based, health

workers. All three models mobilize their respective CFL “provider”—i.e. the mentor mother, expert clients, or CHW—to trace HIV-positive women and HEIs who fall out of care, and encourage these women and infants to return to the clinic by phone contact or by targeted home visits in the community.

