#### 4.0 Central Hypothesis

Our central hypothesis is that all three CFL models will be associated with increased MIP care retention, maternal viral suppression, and infant 12-month HIV-free survival compared to the standard of care, and that a CFL model featuring CHWs will be shown to be most effective, being associated with a higher proportion of HIV-positive women virologically suppressed and retained in care at 12 months, and infants alive, HIV-free and retained in care at age 12 months compared to other models. We further hypothesize that the following components of CFL models will be significantly associated with MIP retention in care and will constitute the most essential features of effective CFL models: low ratio of clients to CFL provider, high frequency of CFL provider-client interaction (i.e.  $\geq 1$  time per month), early “defaulter tracing” activities, and availability of one-on-one support from CFL providers.

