### 5.2 Objectives

Our research objectives are:

1. To establish a clear typology for CFL models by describing the main components of, and key stakeholder experiences of and perspectives on, 3 common approaches in Malawi.
2. To describe MIP health outcomes in 3 CFL models, and compare outcomes across models and versus the standard of care using an epidemiologic sampling strategy.
  - 2a. To examine associations between individual components of CFL models and MIP health outcomes, controlling for confounding.

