follow-up (LTFU) to the national PMTCT/ART program (defined by the MOH as all those who have not returned to the clinic for more than 2 months after the date when they were expected to run out of antiretrovirals and are not documented as having transferred out, stopped ART, or died); 2) mortality is 30% among HIV-infected mothers who are LTFU; and 3) a coefficient of variation of 0.15 should be adequate to obtain relatively conservative projections of precision in each joint stratum. Applying these considerations to our MIP target population, we will select between 66% and 100% of high-volume sites and about 30 MIPs at each site from across the 20 joint strata to enrol our nested cohort (**Table 3**).

**Table 3:** Illustrative sampling approach for individual mother-infant pairs at facility catchment area level.

| Joint stratum number | Total high-volume catchment areas in strata | Expected catchment areas sampled (66 - 100%) | Expected Range of number of PMTCT mothers available for sampling per joint stratum | Approximate Total Mothers sampled | Approximate Mothers with complete routine care data (.73 SOC, .80 CFLs) | Approximate Mothers Needing Tracing (0.27 SOC, 0.20 CFLs) |
|----------------------|---------------------------------------------|----------------------------------------------|------------------------------------------------------------------------------------|-----------------------------------|-------------------------------------------------------------------------|-----------------------------------------------------------|
| 1*                   | 0                                           | 0                                            | 0                                                                                  | 0                                 | 0                                                                       | 0                                                         |
| 2                    | 0                                           | 0                                            | 0                                                                                  | 0                                 | 0                                                                       | 0                                                         |

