We will explore associations between CFL model and individual-level maternal care retention and infant HIV-free survival at 12 and 24 months using multivariate log binomial regression modelling. We will estimate the effect of receiving any CFL service on the risk of 12-month maternal LTFU and viral suppression, controlling for other measured individual- and catchment area-level covariates, including age, pregnancy number, district, facility type, and number of women registered in the PMTCT cohort, among others; we will conduct a sub-group analysis for women who initiated ART while breastfeeding. We will repeat this analysis to examine effects of CFL model components—including client-to-provider ratio, frequency of provider-client interaction, pro-active versus reactive visit adherence approach, presence of CFL provider remuneration, CFL provider training frequency and duration, availability of one-on-one psychosocial support, and other variables—on maternal 12-month LTFU, maternal viral

suppression, and infant 12- and 24-month HIV-free survival. For maternal viral suppression, we will use survival analysis methods to control for variability in the timing of outcome ascertainment and to enable comparison of viral suppression between groups accounting for interval censoring. For the 24-month HIV-free survival outcome, we will control for infants who do not reach 24 months of age by the time of outcome ascertainment by excluding them from the analysis (so that the outcomes for all infants are represented by those who made it to 24 months in the study). As a check on the robustness of this approach, we will conduct a sensitivity analysis and use inverse probability weighting of those with outcomes at 24 months (compared to the total study sample) to account for any potential differences between infants who have and do not have a 24-month outcome at the time of field outcome ascertainment. Risk differences, unadjusted risk ratios, and adjusted risk ratios with accompanying 95% confidence intervals will be estimated for each model. Of note, these estimates will include the MIPs lost to routine care who are traced through the study, therefore allowing for more robust estimates of true outcomes in the study cohort.

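### The two return-to-care outcomes count only clients already out for 2 months, so on their own they cannot compare how well models bring defaulters back

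*Protocol*

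**What the plan says.** Section 7.1 of the protocol lists two return-to-care outcomes among its secondary outcomes.

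- **Mothers and infants under the ART programme.** The proportion who came back "within 30 and 60 days of meeting the national ART program definition of loss to follow-up". The definition excludes known transfers, stops and deaths and requires that clients "have not returned to the clinic for 2 months after the woman is expected to have run out of ARVs".
- **HIV-exposed infants (HEIs) under the HIV Care Clinic programme.** The same 30- and 60-day windows. The definition requires that they "have not returned to the clinic for 2 months after the" next appointment date given at the last visit.

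Section 6.4.1 describes the national rule in nearly the same terms ("have not returned to the clinic for more than 2 months after the date when they were expected to run out of antiretrovirals").

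Objective 2 in section 5.2 is to describe outcomes in the three models and to "compare outcomes across models and versus the standard of care using an epidemiologic sampling strategy". Section 4.0 names among the features expected to be most essential "early “defaulter tracing” activities, and availability of one-on-one support from CFL providers". Section 7.2.2.1 lists "pro-active versus reactive visit adherence approach" among the model components to be analysed. Section 2.0 says that all three models use their providers "to trace HIV-positive women and HEIs who fall out of care".

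**The concern.** Two clients show the problem. One runs out of drugs and is brought back on day 20. She never meets the LTFU definition and does not appear in the outcome at all. Another is left until day 65 and then returns. She counts as a success.

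Being in the denominator is thus an event after exposure to the model, and tracing is designed to prevent that event. If early tracing recovers the clients who are easier to bring back, those who remain in that model's denominator are on average harder to bring back than under standard of care. The 30- and 60-day proportions then mix two things: how well lost clients are returned, and which clients were allowed to become lost.

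No listed outcome measures return before the 2-month point. A reader who takes these two proportions as a league table of tracing could rank the models wrongly.

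**Working it through.** The protocol states no figure for return to care, so there is none to reproduce. The exclusion of early returners follows from the definitions alone. The arithmetic below asks only which way the outcome can move. All return rates in it are assumptions.

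**Illustration 1: two kinds of client.** Take 1,000 clients who pass the run-out or appointment date. Assume 600 are easier to return and 400 harder. Among the harder, 10% return before 2 months, and 10% of the rest return in the next 60 days. Among the easier, a share e returns before 2 months and 50% of the rest return in the next 60 days. Let m multiply both post-LTFU probabilities.

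- Lost = 600(1 − e) + 400 × 0.9
- Returned in 60 days = m × [600(1 − e) × 0.5 + 360 × 0.1]
- Outcome as defined = returned / lost
- Back by about 4 months = (1,000 − lost + returned) / 1,000

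Standard of care, e = 0.4, m = 1: lost = 360 + 360 = 720; returned = 180 + 36 = 216; outcome = 216/720 = 30.0%; back = (280 + 216)/1,000 = 49.6%.

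| e | m | Lost | Returned in 60 days | Outcome as defined | Back by about 4 months |
|---|---|---|---|---|---|
| 0.4 (standard of care) | 1 | 720 | 216 | 30.0% | 49.6% |
| 0.6 | 1 | 600 | 156 | 26.0% | 55.6% |
| 0.8 | 1 | 480 | 96 | 20.0% | 61.6% |
| 0.9 | 1 | 420 | 66 | 15.7% | 64.6% |
| 0.8 | 1.25 | 480 | 120 | 25.0% | 64.0% |
| 0.8 | 1.5 | 480 | 144 | 30.0% | 66.4% |
| 0.8 | 2 | 480 | 192 | 40.0% | 71.2% |

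More clients are back in every row below the first. The outcome as defined is lower, equal or higher.

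**Illustration 2: continuous variation between clients.** Each client has a daily return rate r, lognormal with median 0.005 and log-scale SD 1. The model multiplies r by a in days 0 to 60 and by b afterwards.

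- Outcome = E[exp(−60ar)(1 − exp(−60br))] / E[exp(−60ar)]
- Back by day 120 = 1 − E[exp(−60ar − 60br)]

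Standard of care (a = b = 1): outcome 24.4%, back by day 120 48.5%. With a = 2:

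| b (effect after 2 months) | 60-day outcome | Against 24.4% |
|---|---|---|
| 1 | 20.6% | lower by 3.8 points |
| 1.1 | about 22% | lower |
| 1.25 | 24.6% | about level |
| 1.5 | about 28% | higher |
| 2 | about 35% | higher by more than 10 points |

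In the b = 1 row, 59.1% are back by day 120, about 11 points better than standard of care. With b held at 1, a from 1.5 to 3 and SD 1 to 1.5, the outcome falls 2 to 8 points below standard of care.

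**Identical clients (SD 0), b = 1.** The outcome is 1 − exp(−60 × 0.005) = 25.9% whatever a is. The share back by day 120 rises from 1 − exp(−0.6) = 45.1% to 1 − exp(−0.9) = 59.3% when a = 2. Here the outcome does not register the benefit at all.

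**The case against.** The case on the other side is substantial, and most of it stands.

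- **Direction.** A reader might infer that a model with good early tracing will score worse. The documents do not support that. It happens only if clients differ in how easily they return and the model adds little after 2 months. Section 2.0 has all three models tracing people who have fallen out of care, and section 7.1 treats defaulting and the 2-month definition as the same thing, so an effect after LTFU is plausible. If it is large enough, the CFL model scores better.
- **Role of the outcome.** A reader might also infer that these two outcomes are the protocol's test of early tracing. They are not named in section 7.2.2. The early-tracing hypothesis in section 4.0 is about retention, and the component analysis in section 7.2.2.1 is specified for 12-month LTFU, viral suppression and infant HIV-free survival. The link to comparing models is the general wording of Objective 2.
- **Early return is credited elsewhere.** Section 7.2.2.1 calculates retention among all eligible women from the start of the cohort, and 12-month LTFU is modelled directly. A woman brought back on day 20 counts favourably in both. But neither shows whether or when defaulters were returned.
- **Any later starting point is also selected.** Pro-active support can prevent the missed date itself, so an overdue denominator is not free of the problem. It also takes in clients a day late who return unprompted. This is why the overdue-based measure should supplement the national-definition outcome, not replace it.

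None of this removes the central fact: the conditional proportion never credits a return before 2 months, and its denominator differs by model for reasons the model itself influences.

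**Conclusion.** The point holds in this form: the two return-to-care proportions condition on an event that tracing changes. A model with effective early tracing can score worse, the same or better, depending on its effect after LTFU and on how clients differ. Taken alone, they cannot be read as tracing effectiveness across models.

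The size is not known from the protocol. Under the assumed rates with early return doubled, the 60-day outcome runs from 3.8 points below standard of care to more than 10 points above it, although more clients are truly back in every case. These figures illustrate and do not predict.

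The scope is limited to two of the thirteen listed secondary outcomes. The primary outcome, 12-month maternal retention, does not use this denominator and is unaffected. Using the national definition is a sound reason to report the proportion, but not a sufficient basis for comparing models on it.

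**What to change.** Keep the proportion under the national definition as it stands. For any comparison between models, amend section 7.1 and the analysis text in section 7.2.2.1 as follows.

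1. Report beside it, by model, the proportion of all clients in the cohort who reach the LTFU definition.
2. Add the cumulative incidence of return among all clients overdue from the expected drug run-out date (next appointment date for exposed infants), at 30, 60, 90 and 120 days, with death and transfer as competing events.
3. State that becoming overdue can itself be affected by pro-active visit support, and read item 2 together with the proportion who become overdue.

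This concerns measurement only and changes no programme rule. The current outcomes already need run-out, appointment and return dates, so no new data item is required. The cost is slightly more analysis and a comparative figure that no longer starts at the national LTFU point.

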## 7.2 Analysis Plan by Objective

### 7.2.1 Analysis Plan for Objective 1

#### 7.2.1.1 Survey Data

We will present proportions for CFL components that can be presented as categorical variables, such as: the proportion of facility catchment areas with observed, practicing CFL providers (i.e., expert clients, mentor mothers, or CHWs); proportion of catchment areas with more than one CFL model observed operating; proportion of CFL providers in selected facility catchment areas who are remunerated; proportion of facility catchment areas offering one or more women’s support groups; proportion of facility catchment areas offering one-on-one client counselling; proportion of facility catchment areas providing follow-up after a missed visit (e.g., by phone call, SMS, or home visit); among others. For CFL components that are best summarized as continuous variables, we will calculate means with standard errors or medians with interquartile ranges, as appropriate, for such variables as: average number of CFL providers per facility catchment area; average number of clients per CFL provider; average CFL provider catchment area population size; average number of CFL encounters provided to clients per month; average number of “defaulter” tracing contacts with clients per month; average number of CFL provider contacts with clients during the first 3 months post-ART initiation; average mentor mother/ expert client/ CHW remuneration; etc. We will compare characteristics between CFL models using the Chi-square and Fisher’s Exact test for categorical variables, and the Student’s t-test and one-way ANOVA for normally distributed continuous variables. For other continuous variables, we will use the nonparametric Wilcoxon Rank-sum test and Wilcoxon Signed-rank test as appropriate.

